## Abstract

**Introduction:**

Reducing meat consumption could contribute towards preventing some chronic conditions and protecting the natural environment. This study will examine the effectiveness of a behavioural intervention to reduce meat consumption.

**Methods and analyses:**

Replacing meat with alternative plant-based product is a randomised controlled trial comparing a behavioural intervention to reduce meat consumption with a no intervention control condition. Eligible volunteers will be recruited from the general public through advertisement and randomised in a 1:1 ratio to receive no intervention or a 4-week intervention comprising the provision of free plant-based meat alternatives, written information on the health and environmental benefits of eating less meat, success stories of people who reduced their meat consumption and recipes. The primary outcome is the change in meat consumption at 4 weeks (T1) from baseline. Secondary and exploratory outcomes include changes in meat consumption at 8 weeks (T2) from baseline and changes from the baseline to both follow-up in other aspects of participants diet, putative psychosocial determinants of eating a low meat diet and of using meat substitutes and biomarkers of health risk, including blood lipid profiles, blood pressure, weight and body composition. Linear models will be employed to explore whether the changes in each of the aforementioned outcomes differ significantly between the control and intervention group. Qualitative interviews on a subsample of participants receiving the intervention will evaluate their experiences of the intervention and help to identify the mechanisms through which the intervention reduced meat consumption or the barriers preventing the intervention to aid this dietary transition.

**Ethics and dissemination:**

The trial has been granted ethical approval by the Medical Sciences Interdivisional Research Ethics Committee (IDREC) of the University of Oxford (Ref: R54329/RE001). All results originating from this study will be submitted for publication in scientific journals and presented at meetings and through the media.

**Trial registration number:**

ISRCTN13180635;Pre-recruitment.

Strengths and limitations of this studyThe first randomised controlled trial assessing the behavioural, nutritional, psychosocial and health impact of a 4-week intervention to reduce meat consumption through replacement with meat alternatives.Assessment of putative psychosocial determinants of meat and meat alternatives consumption will help to identify the active components of the intervention and will help inform future intervention development.Health risk outcomes will provide preliminary evidence on potential health implications of replacing meat with meat alternatives in the diet.Recruitment will occur among adult-only households within Oxford (UK), limiting the generalisability of the results.The study will only provide proof of principle for the short-term effectiveness of a behavioural intervention to reduce meat consumption and future work will be needed to translate these insights into longer term interventions in routine settings.

## Introduction

While meat is a source of important nutrients and can be part of a healthy diet,^1^ red and processed meat consumption is also associated with an increased risk of developing some forms of cancer,^2–4^ cardiovascular disease^5–8^ and type 2 diabetes.^7 9–11^ Furthermore, producing meat can negatively affect the natural environment and contribute to anthropogenic global warming,^12–14^ which may also detrimentally affect human health.^15–18^ Reducing meat consumption couldhelp to promote public health and protect the natural environment, but a recent report identified ‘a remarkable lack of policies, initiatives or campaigns’ designed to tackle the demand for meat.^19^ This state of inaction is partly due to the scarcity of evidence on the effectiveness of interventions to reduce meat consumption^19–23^ warranting more experimental research to develop and evaluate such interventions. The rising availability of alternatives, such as textured vegetable proteins and mycoprotein-based alternatives,^24^ could help to reduce meat consumption, as these products resemble meat in their gastronomic function, appearance and preparation. Nevertheless, uptake of meat alternatives remains low in many developed countries,^24–27^ which might partly be due to a lack of familiarity with these foods.^25 28 29^ Interventions increasing people’s familiarity with meat alternatives could, therefore, help to overcome this barrier and, in turn, reduce meat consumption. A recent systematic review of experimental studies concluded that interventions that supplied plant-based alternatives were associated with reductions in meat consumption during, and several weeks after, the interventions.^23^ Nevertheless, this evidence is based on small uncontrolled pre–post intervention studies^30 31^ and more systematic evaluations of the behavioural impact of such interventions is warranted. Additionally, there is currently no evidence from randomised trials on the psychosocial and health consequences of interventions aiming at reducing meat consumption through the replacement with meat alternatives.

### Objectives

The primary aim of the replacing meat with alternative plant-based products (RE-MAP) trial is to examine the effectiveness of a behavioural intervention to reduce meat consumption compared with a no intervention control condition. Additionally, this study will evaluate the impact of the intervention on the consumption of other food groups, the nutritional composition of participants’ diets, the putative psychosocial determinants of eating a low meat diet and of using plant-based meat alternatives and on biological markers of health risk, including blood lipid profiles, blood pressure, weight and body composition. This study also aims to qualitatively investigate participants’ experiences of the intervention, the mechanisms through which the intervention reduced meat consumption, and/or the barriers preventing the intervention to aid this dietary transition.

## Methods

### Study design and setting

The Re-MAP study will employ a two-arm parallel group individually randomised controlled trial (RCT) to evaluate a 4-week behavioural intervention to reduce meat consumption. The primary endpoint is defined as the change in average daily meat consumption at 4 weeks form baseline, assessed through self-reported 7 days food diaries. The study will be conducted in Oxford, UK.

### Recruitment

Participants will be recruited from the general population through advertisements in public buildings, newspapers, mailing lists and social media. Individuals contacting the study team will receive a written information sheet summarising the study protocol. Individuals confirming their interest will be called by the recruiting member of the research team, who will summarise the study protocol and answer any outstanding question. The recruiting member of the research team will also screen individuals against the eligibility criteria and invite eligible individuals to attend an enrolment appointment.

### Eligibility criteria

Inclusion criteria:Are ≥18 years old.Self-report to eat meat regularly.Belong to an adult-only household.Are willing to try meat alternatives.Own adequate food storing facilities.Possess a device compatible with the requirements of the online food diary.Provide informed consent.

Exclusion criteria:Report they have relevant food allergies.Report suffering from an eating disorder.Report to be pregnant or plan pregnancy in the study period.Belong to the same household as a previously enrolled participant.Report consuming meat alternatives more than once a week on average.Return baseline dietary records of insufficient quality for analysis.The recruiting researcher deems the interested individual unable to adhere appropriately to the study protocol (eg, insufficient knowledge of the English language, planned absences from main residence during the course of the study, enrolled in other longitudinal dietary intervention study).

### Participant flow

#### Enrolment appointment

The enrolment appointment will take place on the university premises. During this appointment, an appropriately trained member of the research team will seek written informed consent (see online supplementary file 1), witnessing this by means of dated signature. After gaining informed consent, the enrolling member of the research team will set up participants’ online food diaries to include six possible meal entries per day (breakfast, mid-morning, lunch, mid-afternoon, dinner and postdinner) and to allow the research team to remotely access participants’ food diaries by means of a password. The recruiting member of the research team will also train participants in how to appropriately use the online food diaries and estimate portion sizes.

10.1136/bmjopen-2018-027016.supp1Supplementary data

#### Baseline

Following the enrolment appointment, participants will complete a 7-day food diary over the week leading up to the following appointment, the baseline (T0). Participants not keeping sufficiently detailed diaries and those eating meat on less than five eating occasions over the week will be discontinued. At the baseline appointment, an appropriately trained member of the research team will collect participants’ food diaries, ask participants to answer the baseline online questionnaire and measure participants blood lipids profile, blood pressure, weight and body composition. At the end of the baseline appointment, participants will be randomised to one of the two study conditions and will then follow the respective protocol for the next 4 weeks.

#### Follow-up

Participants will be invited to attend a 4-week (T1) and an 8-week (T2) follow-up and to keep a 7-day food diary over the week leading up to each follow-up. During the follow-up appointments, a member of the research team will collect the respective food diary, ask participants to answer an online questionnaire and measure participants blood lipids profile, blood pressure, weight and body composition.

### Sample size

Due to lack of research studies directly comparable to ours, pragmatic considerations have guided the decision to terminate recruitment once a sample of at least 100 volunteers has completed the 4 weeks follow-up. A power analysis based on this pragmatically selected sample size suggests that 100 participants completing the primary outcome will allow detection of a medium effect size of d=0.6 with a power of 1-beta=0.84 and a two-tailed alpha criterion of 0.05.

### Randomisation and blinding

Participants’ group allocation will be based on a computer-generated randomisation sequence, produced by an independent statistician. The randomisation sequence was designed to individually allocate participants to the intervention or control condition in a 1:1 ratio and to achieve a proportional gender balance in the two conditions through blocking and stratification by sex. The research team is blinded to the randomisation sequence and to its block sizes and sequence. Allocation will be revealed to the researcher performing the randomisation only after the first food diary has been returned. Due to the nature of the intervention, participants and some members of the research team cannot be blind to participants’ group allocation. The members of the research team analysing the food diaries will be blind to the group allocation. Due to the nature of the outcomes, the risk of investigator bias will be low. To address the risk of social desirability bias in participants’ reporting of foods intake and questionnaire responses, participants will be reminded during the enrolment visit and before each questionnaire that there are no right or wrong answers.

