### Outcomes

#### Primary outcome

Change in mean daily grams of meat consumed between the baseline (T0) and the 4-week follow-up (T1).

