### Statistical analyses

We will employ linear models to investigate whether changes in meat consumption between the baseline and both follow-up differ significantly between the intervention and the control group. Our main analysis will employ unadjusted models and only include data from participants completing the relevant follow-up. Sensitivity analysis will be performed with a baseline observation carried forward assumption for missing data and adjusting for baseline variables. The intervention effect will be reported with 95% CI and p values. A two-tailed criterion p value of alpha=0.05 will be used to assess the statistical significance of the results. The same procedure will be employed to assess whether changes in the other prespecified dietary, nutritional, psychosocial and biophysical outcomes between the baseline and both follow-up differ significantly between the control and the intervention group. Detailed main, subgroup and sensitivity analyses plans will be finalised before conducting any specific outcome analysis. No interim analysis is planned.

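### Randomisation is stratified by sex but the main models leave sex out; if sex predicts the change scores, the confidence intervals are somewhat too wide and the tests conservative

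*Protocol article*

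**What the plan says.** Protocol article, Randomisation and blinding: the sequence is designed "to achieve a proportional gender balance in the two conditions through blocking and stratification by sex". Participants are randomised individually, with equal allocation to the arms. Sex is the only stratification factor named.

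Protocol article, Statistical analyses: "Our main analysis will employ unadjusted models and only include data from participants completing the relevant follow-up". Adjustment appears only in the next sentence: "Sensitivity analysis will be performed with a baseline observation carried forward assumption for missing data and adjusting for baseline variables". The baseline variables are not listed. The section also promises that "The intervention effect will be reported with 95% CI and p values", sets a two-tailed alpha of 0.05, and carries the same procedure over to the dietary, nutritional, psychosocial and biophysical outcomes.

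Detailed analysis plans are deferred to a later document. The unadjusted form of the main model is not deferred; it is stated here.

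**The concern.** Stratified blocks force the two arms to be nearly balanced on sex. The arm difference then no longer varies from one randomisation to the next because of chance sex imbalance. An arm-only linear model does not know this. It treats variation between the sexes as noise and includes it in the standard error.

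If sex is related to the change being analysed, the interval is wider than the design warrants and the test rejects less often than 5% under the null. The precision that stratification was meant to provide is then missing from the primary confidence interval and p value. That matters a little more in a trial of about 100 completers whose size was chosen pragmatically.

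**Working it through.** **Inputs from the protocol.** "100 participants completing the primary outcome" (Sample size), hence 50 per arm under 1:1 allocation; d = 0.6; power 0.84; two-tailed alpha 0.05.

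**Assumptions, not in the protocol.** R², the share of variance in the change score explained by sex, is varied over 0, 2%, 5%, 10% and 20%. The simulations use blocks of 4 and a 50/50 sex mix, with a check at 70/30.

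**Step 1: the plan's own figure.** A two-sample t test with 98 degrees of freedom and noncentrality 0.6 × √(50/2) = 3.0 has power 0.844. The normal approximation gives 0.851. The stated 0.84 is reproduced, and it refers to an unadjusted comparison.

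**Step 2: reported against true standard error.** With the outcome SD set to 1 and N = 100:
- The arm-only model reports about √(4/100) = 0.200.
- With exact balance on sex, the true value is √(4(1 − R²)/100).
- The interval is too wide by the factor 1/√(1 − R²).
- The actual type I error is 2 × [1 − Φ(1.96/√(1 − R²))].

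| Assumed R² | True SE | Width factor | Type I error, formula | Type I error, simulated | Simulated with sex in model |
|---|---|---|---|---|---|
| 0 | 0.200 | 1.000 | 0.050 | 0.050 | 0.051 |
| 2% | 0.198 | 1.010 | 0.048 | 0.048 | 0.050 |
| 5% | 0.195 | 1.026 | 0.044 | 0.046 | 0.052 |
| 10% | 0.190 | 1.054 | 0.039 | 0.039 | 0.050 |
| 20% | 0.179 | 1.118 | 0.028 | 0.028 | 0.051 |

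The simulations used 20,000 replicates, so their standard error near 0.05 is √(0.05 × 0.95/20,000) ≈ 0.0015. With a 70/30 sex mix, the unadjusted type I error was 0.045 at 5% and 0.028 at 20%.

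**Step 3: power at d = 0.6.** Simulated with 8,000 replicates, without and with sex in the model:
- R² = 5%: 0.840 and 0.852
- R² = 10%: 0.844 and 0.870
- R² = 20%: 0.872 and 0.915

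The unadjusted test does not fall below the stated 0.84 by more than rounding. What is given up is a possible gain.

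**Step 4: what each R² would require.** With equal numbers of men and women, the sex gap in change, in within-sex SDs, is 2 × √(R²/(1 − R²)). This gives 0.29 at 2%, 0.46 at 5%, 0.67 at 10% and 1.0 at 20%. At 10% the gap is already larger than the whole treatment effect the trial is powered to detect (0.6).

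**Step 5: completers only.** Dropout loosens the exact balance. With an assumed 15% random dropout, the simulated type I error for 2%, 5%, 10% and 20% was 0.048, 0.045, 0.042 and 0.032. A repeat run gave 0.048, 0.045, 0.038 and 0.030. The shift towards 0.05 is small and, below 20%, hard to separate from simulation error.

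**The case against.** The strongest objection is that the discrepancy depends on the outcome. If sex does not predict the change, the unadjusted standard error is right and nothing is lost. This stands, so the point is conditional. A reader might infer that the reported intervals and p values are wrong as a matter of fact. The protocol does not support that, because it gives no association between sex and any change score.

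A second tempting inference is that outcomes such as energy intake, HDL cholesterol or body fat must be badly affected because men and women differ on them. Those are differences in level. The outcomes listed in the protocol are changes from each participant's own baseline, and a stable difference in level cancels. This also stands, and it makes the upper rows of the table demanding. The type I figures at 10% and 20% apply under the null and so require untreated men and women to differ by 0.67 to 1.0 SD in change.

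Third, the error is in the safe direction and the promised power is delivered. Correct; this limits the priority of the point but does not remove it.

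Fourth, a sensitivity analysis with baseline variables is planned, sex is collected at baseline (Sociodemographic characteristics), and detail is deferred. An unnamed covariate list is fair to leave to the later plan. But that analysis, even with sex in it, would not change the primary interval and p value, which come from a model the protocol already fixes as unadjusted.

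**Conclusion.** The point holds in a limited, conditional form. The protocol stratifies by sex and fixes main models that ignore it, so the reported inference takes no account of the design to the extent that sex predicts change. The treatment estimate is not biased, false positives are not inflated, and neither the sample size nor the stated power needs revision.

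The size rests on an R² that the protocol does not give. It is zero if sex is unrelated to change and slight at 2% to 5% (Step 2). The 10% and 20% rows are an upper bound rather than an expectation. This is an inexpensive improvement in precision and calibration, not a threat to the trial's conclusions.

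**What to change.** In the main linear models for the primary, secondary and exploratory outcomes, include sex, as used for stratification, as a prespecified fixed covariate. Report the model without sex as a sensitivity analysis. State this in the detailed analysis plan before any outcome analysis.

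The cost is one model term and one degree of freedom (97 instead of 98 with 100 completers). No new data are needed, since sex is required for stratified allocation and recorded at baseline. In the simulations, power with sex included was essentially equal at R² = 0 (0.848 against 0.849) and higher at every R² above zero.

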### Intervention and comparator

#### Intervention

Re-MAP is a 4-week behavioural intervention, which aims to reduce meat consumption, defined as non-seafood meat products, among regular meat eaters. Following an analysis of the target behaviour, that is, a reduction in meat consumption, we included five psychosocial variables as the intervention’s targets: attitudes, perceived behavioural control and subjective social norms of eating a low meat diet, as well as attachment to meat, and eating identities (eg, ‘meat eater’ or ‘vegetarian’). We then selected four intervention functions from the Behaviour Change Wheel^32 33^ with the aim of influencing these psychosocial variables^1^: environmental restructuring enacted through providing meat alternatives for 4 weeks,^2^ training enacted through recipes,^3^ education enacted through infographics on the health and environmental benefits of eating less meat, and^4^ social modelling enacted through written vignettes outlining the story of people who reduced their meat consumption. These success stories were developed following an online patient and public involvement (PPI) activity. This PPI activity involved asking people who consciously reduced their consumption of meat to share their motives to do so, their strategies to enact this dietary transition, and the way they overcame the challenges associated with this transition. A logic model of the intervention is displayed in figure 1.

**Figure 1 F1:**
[figure not shown]
Intervention logic model.

### Comparator

Participants in the control condition will receive no intervention. The template for intervention description and replication (TiDIER) checklist^34^ for the Re-MAP intervention and the comparator is reported in table 1.

**Table 1 T1:** TiDIER checklist describing the replacing meat with alternative plant-based product (Re-MAP) intervention and no-intervention comparator

	Intervention	Comparator
Brief name	Re-MAP—a behavioural intervention to reduce meat consumption	No intervention
Why	Environmental restructuring: Meat alternatives will be provided for 1 month with the aim of enhancing attitudes towards and behavioural control of eating a low meat diet by making meat-free alternative easily available to participants. This intervention component also aims to reduce participants’ attachment to meat. Participants will select from a range of commercially available meat alternatives including soy and other textured vegetable protein products (eg, soy sausages), plant-based and pulse-based products (eg, bean burgers), mycoprotein products (eg, mycoprotein steaks). Meat alternatives will be defined as meat-free products that fulfil the same gastronomic function as products that normally contain meat (eg, sausages, burgers, meatballs, steaks or mince). Training: Recipes will be provided with the aim of enhancing participants’ behavioural control of eating a low meat diet by enhancing their skills of preparing meat-free meals. Education: Information leaflets about the health and environmental benefits of eating less meat will be provided to enhance participants’ attitudes towards eating a low meat diet and to reduce participants’ attachment to meat. Social modelling: Written success stories of people who reduced their meat consumption will be provided to increase participants perceived social norm of eating a low meat diet and to promote the dietary identity of meat reducers, such as flexitarians.	N/A
What	Environmental restructuring: Participants will be provided with meat alternatives for 1 month, which they will be able to select from a printed catalogue of commercially available meat alternatives. Participants will be asked to select enough meat alternatives to have a meat-free product available on every occasion on which they would normally have meat for 2 weeks. Participants will be free to order enough foods to cater for themselves and other members of their household, if they wished to do so. The meat alternatives will be delivered to participants’ homes by a food retailer on up to two occasions over the intervention month: the first delivery will be scheduled immediately after participants are allocated to the intervention condition. The second delivery will be scheduled 2 weeks after the randomisation for participants who wish to top up their stock of meat alternatives. Training: A printed booklet containing 11 illustrated recipes of meat alternatives will be delivered immediately after participants are allocated to the intervention condition. These recipes will incorporate some of the meat alternatives used as part of this study. A second cookbook predominantly reporting on more general meat-free recipes (ie, not focussing on meat alternatives) will be provided during the fourth intervention week. All participants received the same recipes. Education: Participants will receive eight printed pages of illustrated information on the health (four pages) and environmental implications(four pages) of eating less meat and two introduction pages and references delivered per post to their home over the course of the intervention month. The infographics were developed using publicly available information from peer-reviewed literature and relevant environmental or health organisations (eg, cancer research UK). Immediately after being allocated to the intervention condition, participants will receive an illustrated binder, which they will use to collect the information leaflets. The binder will include two pages of introductory information and the sources from which the information was drawn. Success stories: Participants will receive three illustrated success stories vignettes delivered per post to their home during the last intervention week. The success stories will cover a range of different demographics (sex and age), different motives for eating less meat, and different strategies to transition to lower meat diets. The narratives will be about eating less meat rather than about ceasing to eat meat entirely. Participants will also receive a sheet on which they could report their own success story if they wish to do so. Participants will be asked to add this information to their illustrated binder.	N/A
Who	The lead researcher of this trial (FB) will deliver the intervention. An access database system will be used to schedule the deliveries of each intervention component ensuring that each intervention component will be delivered at the appropriate time for each participant.	N/A
How	The intervention consists in the delivery of the aforementioned materials. We will use the delivery services of one of UK’s largest food retailers to purchase and deliver the meat alternatives to participants. We will use Royal Mail to send printed materials. The binder will be delivered to participants immediately after they are randomised to the intervention condition.	N/A
Where	N/A	N/A
Tailored	N/A	N/A
How well	We elected to use a single study account with the food retailer to schedule all the study deliveries, which will enable us to monitor the successful completion and receipt of each delivery. Due to the nature of the intervention, it will not be necessary to establish any other systems to monitor the fidelity of the intervention delivery.	N/A

N/A, not available; TiDIER, template for intervention description and replication.

